### **8.6 Safety Analyses**

Adverse events (AEs) and serious adverse events (SAE) (comp. Sections 6.3), will be listed summed by occurrence, severity (comp. Section 6.3.1.2.1), outcome, and causal relationship to treatment (comp. Section 6.3.1.2.2) and will be descriptively compared between the two treatment groups using Fishers exact test. Associated AE tables present the total number of patients reporting at least one specific event and the maximum severity grade (patients reporting more than one episode of the same event are counted only once by the maximum severity and highest causality). Special tables will be displayed for MACE (comp. Section 6.3.1.6) and for AEs leading to withdrawal.

In addition, summary tables with patient identification will be presented. The tables provide the numbers and percents of patients with AEs, and also include the subject identification in the table.

Separate summarizations of AEs by worst severity, and of SAEs and AEs that are likely related to treatment and AEs that are unlikely related to treatment (comp. Section 6.3.1.2.2) will also be provided. All AEs will be listed.

Descriptive statistics for laboratory parameters (comp. Table 1, Section 6.3.2.1) will be presented by treatment group and time point. For continuous laboratory parameters, changes from baseline to the other time points will be presented by treatment group and descriptive statistics will be calculated.

Values will also be presented according to the CTC categories. Values outside corresponding normal ranges will be displayed and tabulated.

A new abnormality is defined as an out-of-range value that was previously normal or a value that is initially out of range in one direction (either low or high) and becomes out-of-range in the opposite direction at the end of the period. A worsened abnormality is a value that was out of range at the start and became more abnormal during the period. Should the rate of new or worsened abnormalities be deemed excessive, further examination of the nature of the abnormalities will be performed.

Changes in vital signs (comp. Section 6.3.2.2) and electrocardiograms will also be examined for treatment group differences.

## 8.7 Determination of Sample Size

Considerations for determining the sample size of the primary efficacy parameter LVEF at 6 months postoperatively, measured by MRI at rest, were carried out on the basis of the results of a previous efficacy pilot trial with  $n=20$  patients per group conducted in Rostock by [name] and co-workers (Stamm et al, 2007). For LVEF at 6 months postoperatively the results were  $47.1 \pm 7$  for patients of the CABG & cell injection group and  $41.3 \pm 8$  for patients of the CABG only group.

The stratification of the primary analysis by center is neglected in the sample size calculation. Instead of the analysis of covariance (ANCOVA) to be used in the primary analysis, the two-sample  $t$  test scenario with equal variances is considered.

Sample size determination is done under the assumption of a two-sided type I error ( $\alpha$ ) at 5% and a type II error ( $\beta$ ) at 10% (i.e. a power at 90%). Since there is some uncertainty regarding the expected means and standard deviations Table 3 presents how many patients per group are necessary for several scenarios, e.g. to show a difference of 3.5 to 5.5 between the two groups.

The scenario of a difference of about 4 to 5 is considered as a clinical relevant difference. With a difference of 4.5 and a standard deviation of 7.5, at least  $n=60$  patients per group are necessary and with an additional 15% drop-out rate a total of at least 142 patients will be randomized.

For  $n=60$  patients per group, Table 4 presents the power for some other scenarios of mean and standard deviation.

Sample size calculation was done using the commercial program nQuery Advisor 5.0, section 8, table MTT0-1 [Elashoff, 2002]. Computation was realized using central and non-central  $t$ -distribution where the non-centrality parameter is  $\sqrt{n} \delta / \sqrt{2}$  and  $\delta$  is defined as effect size  $|\mu_1 - \mu_2| / \sigma$  [O'Brien RG, Muller KE, 1993].

**Table 3: Number of Patients Necessary to Show Differences of the Primary Efficacy Parameter LVEF at 6 Months Postoperatively (Two-Sided,  $\alpha = 0.05$ ,  $1 - \beta = 0.90$ )**

| LVEF 6 months postoperatively
Difference of means between CABG & cell injection group
and CABG only group (standard deviation within both
groups) | Number of patients per
group |
|------------------------------------------------------------------------------------------------------------------------------------------------------------|---------------------------------|
| 3.5 (7)                                                                                                                                                    | 86                              |
| 3.5 (7.5)                                                                                                                                                  | 98                              |
| 3.5 (8)                                                                                                                                                    | 111                             |
| 4 (7)                                                                                                                                                      | 66                              |
| 4 (7.5)                                                                                                                                                    | 75                              |
| 4 (8)                                                                                                                                                      | 86                              |
| 4.5 (7)                                                                                                                                                    | 52                              |
| 4.5 (7.5)                                                                                                                                           | 60                       |
| 4.5 (8)                                                                                                                                                    | 68                              |
| 5 (7)                                                                                                                                                      | 43                              |
| 5 (7.5)                                                                                                                                                    | 49                              |
| 5 (8)                                                                                                                                                      | 55                              |
| 5.5 (7)                                                                                                                                                    | 36                              |
| 5.5 (7.5)                                                                                                                                                  | 41                              |
| 5.5 (8)                                                                                                                                                    | 46                              |

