**Figure 2: Echocardiographic Data**

Echocardiographic data of patients included in the safety trial (n=15). Compared with the preoperative (preop) data, left ventricular ejection (LVEF) fraction rose significantly in response to CABG and CD133+ cell injection ( $p < 0.05$ ) at discharge, 6 and 18 months.

**Efficacy trial:** Forty patients were randomly assigned to undergo either CABG & cell injection or CABG only. All but one patient who remained in the study had an uneventful postoperative course. The only early postoperative complication was a low cardiac output syndrome with acute renal failure in one patient, requiring medium-dose catecholamine treatment and temporary hemofiltration. This patient recovered completely and was transferred to the ward on postoperative day 6. During the follow-up period, no major adverse events (death, myocardial infarction, or cardiac re-intervention) were reported, and all patients were alive and well at most recent follow-up (Dec 31, 2005).

The echocardiographic data on LV function summarized in the data relevant for the primary outcome parameter, “LVEF at 6 months” are depicted in Figure 3. The average LVEF rose from  $37.4 \pm 8\%$  to  $47.1 \pm 8\%$  at 6 months in patients receiving CABG & cell injection ( $p=0.005$ ), and from  $37.9 \pm 10\%$  to  $41.3 \pm 8\%$  in patients undergoing CABG only ( $p=0.47$ ). As required by the study protocol, direct comparison of the primary outcome parameter (average LVEF at 6 months) achieved a p-value of 0.04. Within the range of probability defined by the statistical power, the null hypothesis is therefore rejected, indicating that CABG & cell injection resulted in better LVEF than CABG only. The average change in LVEF was +9.7% in CABG & cell injection patients and +3.4% in CABG only patients ( $p=0.0009$ ).

[figure not shown]

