## 8.8 Interim Analysis

An interim analysis will be performed on the first 70 patients randomized and followed-up for at least 6 month using the adaptive two-stage approach described by Bauer and Köhne, 1994.

At the first interim analysis the null hypothesis  $H_{01}$  can be rejected if

$$p_1 \leq \alpha_1,$$

where  $p_1$  is the (one-sided) p-value from the t-test and  $\alpha_1$  the critical value.

The trial will be stopped for futility if

$$p_1 \geq \alpha_0,$$

where  $\alpha_0$  is the stopping boundary for futility.

If the trial will be continued reassessment of the sample size will be performed.

At the second stage the null hypothesis  $H_{02}$  can be rejected if

$$p_2 \leq \alpha_2,$$

where  $p_2$  is the (one-sided) p-value from the t-test and  $\alpha_2 = c_\alpha / p_1$ .

The sample size  $n_2$  for the second stage will be assessed by considering observed variability and effect of the first stage.

At the end of the trial the null hypothesis  $H_0$  will be rejected if

$$p_1 \cdot p_2 \leq c_\alpha$$

where  $c_\alpha$  is the critical value for the combination test.

The effect size of the primary efficacy parameter will be calculated in a semi-blinded manner. The sample size calculation for the second step will be performed using ADDPLAN (Wassmer & Eisebitt, 2001).

Overall  $\alpha$ -level = 0.025 (one-sided),  $\alpha_0 = 0.5$ ,  $\alpha_1 = 0.0102$ ,  $c_\alpha = 0.0038$

The following secondary endpoints will be evaluated descriptively at the first stage:

- Change in LVEF at 6 months post-OP compared with preoperatively (screening) assessed by echocardiography
- Change in physical exercise capacity determined by 6 minute walk test at 6 months compared with preoperatively
- Change in NYHA and CCS class at 6 months post-OP compared with preoperatively

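### Section 8.7 plans on a pilot SD that section 1.1.2.5 contradicts, and states 90% power for a single-stage test that section 8.8 has replaced

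*Protocol*

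**What the plan says.** Section 8.7 builds the sample size on a pilot with 20 patients per group:

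- Cell arm, LVEF at 6 months: "47.1 \pm 7$ for patients of the CABG & cell injection group".
- Control arm: mean 41.3, SD 8.
- Error rates: "Sample size determination is done under the assumption of a two-sided type I error" of 5%, with a type II error of 10% ("i.e. a power at 90"%).
- Chosen scenario: "With a difference of 4.5 and a standard deviation of 7.5, at least" 60 per group, raised to 142 in total for 15% drop-out.
- Method: a two-sample t-test with equal variances, in place of the ANCOVA planned for the primary analysis.

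Section 1.1.2.5, in the efficacy-trial paragraph after Figure 2, reports the same pilot arm at the same time point as "47.1 \pm 8\%$ at 6 months in patients receiving CABG & cell injection". The control arm is again 41.3 with SD 8.

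Section 8.8 then adds a second layer: "An interim analysis will be performed on the first 70 patients randomized and followed-up for at least 6 month", with the Bauer and Köhne two-stage method. The boundaries are alpha_1 = 0.0102, alpha_0 = 0.5 and c = 0.0038, at an overall one-sided level of 0.025. The second-stage size is to be set from the variability and effect observed in stage 1. Section 1.3 explains that this interim analysis was appended after a later phase II trial of the same cell type missed its primary endpoint.

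**The concern.** The two descriptions of the pilot cannot both be right: one arm, one mean, one time point, two SDs. The planning SD lies between 7 and 8, so the choice of pilot value bears directly on whether 7.5 is a central assumption or an optimistic one.

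The power statement in section 8.7 was also left as it stood when section 8.8 was added. A two-stage product test that can stop for futility does not have the same power as one t-test on the same total, so the 90% describes an analysis that no longer decides the trial. A sponsor, ethics committee or regulator who reads section 8.7 takes 90% as the property of the planned 142 patients.

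**Working it through.** **Inputs.** Difference 4.5; SD 7.5 (section 8.7) or 8 (section 1.1.2.5 for both arms); 60 evaluable per arm; two-sided 5%; boundaries from section 8.8.

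**1. The plan's own figure.** Non-central t with 2n − 2 degrees of freedom and non-centrality √(n/2) × difference/SD. At n = 60 and SD 7.5 this is √30 × 0.6 = 3.29, and power is 90.3%. The smallest n that reaches 90% is 60, and 60/0.85 rounds up to 71 per arm, or 142. All 15 rows of Table 3 reproduce exactly, and Table 4 agrees within one point. The calculation is right for its stated inputs.

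**2. The pilot SD.** With equal arms the pooled SD is √((SD₁² + SD₂²)/2).

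- 7 and 8: √((49 + 64)/2) = 7.52
- 8 and 8: √((64 + 64)/2) = 8.00

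Section 8.7 does not say how 7.5 was derived, but it matches the first line and not the second.

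**3. Effect of SD alone, single stage.** At SD 8 the non-centrality is √30 × 0.5625 = 3.08 and power is 86.3%; 90% needs 68 per arm. The protocol prints both (86 in Table 4, 68 in Table 3).

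**4. Effect of the two-stage test.** The level is correct: 0.0102 + 0.0038 × ln(0.5/0.0102) = 0.02499.

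Power is the probability that p₁ ≤ 0.0102, plus the probability that 0.0102 < p₁ < 0.5 and p₁ × p₂ ≤ 0.0038. It was obtained by integrating over the stage 1 t statistic. Stage 1 is 70 patients with 6-month follow-up, taken as 35 per arm. The remaining 25 per arm bring the total to 60 evaluable.

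| SD | Reject at stage 1 | Reject at stage 2 | Two-stage power | Single-stage power |
|---|---|---|---|---|
| 7.5 | 55.6% | 32.7% | 88.3% | 90.3% |
| 8 | 49.5% | 34.4% | 83.9% | 86.3% |

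Simulation of the 35+25 case gives 88.4% and 84.0%.

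**5. Sensitivity to the split.** If drop-out left only 30 per arm evaluable in stage 1, with 30 in stage 2, the figures would be 88.1% and 83.7%. The split hardly matters.

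**The case against.** **Stage 2 is not fixed.** A reader might infer from the table that the trial as designed has only about 84% power. The documents do not support that. Section 8.8 reassesses the second-stage size from stage 1 data, and 25 per arm is an assumption that holds the total at the planned number. With re-estimation at SD 8, under an assumed 90% conditional-power target and an assumed minimum of 25 per arm, power is about 89%, 95% and 97% for stage 2 caps of 36, 60 and 100 per arm. Section 8.8 states no target and no cap, so none of these is the design's power either. This objection stands, and it is why the restated figures need a label.

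**The SD shortfall is disclosed.** Section 8.7 admits uncertainty about the SD, and Tables 3 and 4 show the SD 8 scenario. This also stands: the calculation uses 7.5, not 7, and only the loss from the two-stage test, about 2 points, appears nowhere. But the tables do not tell the reader that 8 is what section 1.1.2.5 reports for both arms.

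**ANCOVA would recover power.** At SD 8 with 35+25, assumed baseline correlations of 0.3, 0.5 and 0.6 give 87%, 93% and 96%. The protocol gives no correlation, and section 8.8 specifies t-test p-values. The offset is possible but cannot be claimed.

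**Could the pilot SD be larger still?** Section 1.1.2.5 says the pilot comparison ("average LVEF at 6 months) achieved a p-value of 0.04") was significant. A reader might infer an SD near 8.6, since 5.8/(2.127 × √(2/20)) = 8.62. That needs all 20 per arm analysed, an unadjusted equal-variance t-test and p of exactly 0.040. The same paragraph speaks of patients who remained in the study, which suggests attrition. At SD 8, 17 or 18 per arm gives p = 0.042 or 0.037; at SD 7.52, 15 or 16 per arm gives 0.044 or 0.037. All round to 0.04, so the p-value cannot settle the SD. The pilot values in section 1.1.2.5 are also echocardiographic, while the endpoint is MRI.

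**Does the SD feed the interim reassessment?** A reader might think so. Section 8.8 uses the variability and effect observed in stage 1, so no planning SD enters.

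**Conclusion.** The point holds as a correction to section 8.7. The pilot cell-arm SD is given as 7 in one place and 8 in another, and the 90% is for a single-stage test that section 8.8 has superseded. For 4.5 points and 60 evaluable per arm, the two-stage test costs about 2 points of power by itself (90.3% to 88.3% at SD 7.5). Together with an SD of 8 it brings the figure to about 84%.

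These numbers assume equal arms, about 35+25 evaluable per arm, no baseline adjustment and no enlargement of stage 2. They do not show that the adaptive trial is underpowered, and they leave the patient number, the significance level and the decision rule untouched. The documents do not show which pilot SD is correct.

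**What to change.** 1. Check the pilot source data and make sections 1.1.2.5 and 8.7 agree on the cell-arm SD. State in section 8.7 how the planning SD was derived from it.
2. In section 8.7, restate power for the two-stage product test with about 35+25 evaluable per arm (142 randomised) and a 4.5-point difference: about 88% if SD 7.5 is confirmed, about 84% if the SD is 8. Label each figure as t-test power, without baseline adjustment and before any sample-size increase from the interim reassessment.

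The cost is an edit to two sections and a slightly less favourable power statement. No patients are added.

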**Table 4: Power with N=60 Patients per Treatment Group for Several Differences of Means and Standard Deviations**

| LVEF 6 months postoperatively
Difference of means between CABG & cell
injection group and CABG only group
(standard deviation within both groups) | Power     |
|------------------------------------------------------------------------------------------------------------------------------------------------------------|-----------|
| 3.5 (7)                                                                                                                                                    | 77        |
| 3.5 (7.5)                                                                                                                                                  | 71        |
| 3.5 (8)                                                                                                                                                    | 66        |
| 4 (7)                                                                                                                                                      | 87        |
| 4 (7.5)                                                                                                                                                    | 82        |
| 4 (8)                                                                                                                                                      | 77        |
| 4.5 (7.)                                                                                                                                                   | 93        |
| 4.5 (7.5)                                                                                                                                           | 90 |
| 4.5 (8)                                                                                                                                                    | 86        |
| 5 (7)                                                                                                                                                      | 97        |
| 5 (7.5)                                                                                                                                                    | 95        |
| 5 (8)                                                                                                                                                      | 92        |
| 5.5 (7.)                                                                                                                                                   | 98        |
| 5.5 (7.5)                                                                                                                                                  | 97        |
| 5.5 (8)                                                                                                                                                    | 96        |

## 8.8 Interim Analysis

An interim analysis will be performed on the first 70 patients randomized and followed-up for at least 6 month using the adaptive two-stage approach described by Bauer and Köhne, 1994.

At the first interim analysis the null hypothesis  $H_{01}$  can be rejected if

$$p_1 \leq \alpha_1,$$

where  $p_1$  is the (one-sided) p-value from the t-test and  $\alpha_1$  the critical value.

The trial will be stopped for futility if

$$p_1 \geq \alpha_0,$$

where  $\alpha_0$  is the stopping boundary for futility.

If the trial will be continued reassessment of the sample size will be performed.

At the second stage the null hypothesis  $H_{02}$  can be rejected if

$$p_2 \leq \alpha_2,$$

where  $p_2$  is the (one-sided) p-value from the t-test and  $\alpha_2 = c_\alpha / p_1$ .

The sample size  $n_2$  for the second stage will be assessed by considering observed variability and effect of the first stage.

At the end of the trial the null hypothesis  $H_0$  will be rejected if

$$p_1 \cdot p_2 \leq c_\alpha$$

where  $c_\alpha$  is the critical value for the combination test.

The effect size of the primary efficacy parameter will be calculated in a semi-blinded manner. The sample size calculation for the second step will be performed using ADDPLAN (Wassmer & Eisebitt, 2001).

Overall  $\alpha$ -level = 0.025 (one-sided),  $\alpha_0 = 0.5$ ,  $\alpha_1 = 0.0102$ ,  $c_\alpha = 0.0038$

The following secondary endpoints will be evaluated descriptively at the first stage:

- Change in LVEF at 6 months post-OP compared with preoperatively (screening) assessed by echocardiography
- Change in physical exercise capacity determined by 6 minute walk test at 6 months compared with preoperatively
- Change in NYHA and CCS class at 6 months post-OP compared with preoperatively

### Interim analysis for safety

- MACE (cardiac death, myocardial infarction, secondary intervention/reoperation, ventricular arrhythmia).

### Conduct of interim analysis

All staff involved in the interim analysis or with access to the unblinded data should not participate in the conduct of the study or in the blind review of the data at the end of the study. Therefore the unblinded interim analysis will be performed by an independent statistician outside the clinIT AG. [name] who is associated member of the SMB will be appointed as independent statistician. The interim analysis will be performed by [name] in a semi-blind manner. The randomization code of the subjects who will be analyzed in the interim analysis will be provided to the independent statistician by Miltenyi Biotec. The results of the interim analysis will be provided to the steering committee for decision purpose

